### Effect of missing data

This is a comparatively frail population and we can expect some drop-out during the study. It is likely that those participants who are lost to follow-up during the trial may also be people with a tendency to experience poorer quality of life (in terms of fear of falling) than those who remain in the study. In this situation, the data cannot be considered to be missing at random. On the contrary, the event of a patient failing to complete the study may be informative. It is necessary to take into account any difference in drop-out rates and the non-randomness of the drop-out when comparing fear of falling per the FES-I between the two treatment groups. This will be done by jointly modelling ‘survival in the study’ and the repeated measures of fear of falling simultaneously [36] using software that has been developed as part of an MRC-funded programme of work (Grant G0400615; Statistical methodology for longitudinal studies in clinical research; Williamson PR, Diggle PJ and Henderson R). Time to drop-out will be analysed using a Cox proportion hazards model incorporating random effects. Fear of falling will be modelled using mixed models appropriate for repeated measures. A key feature of each of these models is that within each of them it is possible to fit a latent variable that can be conceptualised as the patient’s propensity to experience poor outcomes (both their likelihood to drop out of the study and their likelihood to have poorer FES-I scores). It is the inclusion of this latent variable that allows us to adjust our estimates of the treatment effect to allow for the different rates of drop-out in each group. Both models are estimated simultaneously; parameter estimates are based on maximising the joint likelihood over both the survival and repeated measures data.

### Outcome measures

#### Primary outcome measure

Change in fear of falling as measured by the FES-I [20].

#### Secondary outcome measures

##### Falls

a) Number of patients falling; b) number of falls; and c) fractures and significant soft tissue injuries: the close relationship between fear of falling and falls [5-20,37] means that measurements of falls and their adverse consequences are vital. Falls research is often hampered by poor definitions and hence difficult interpretation of falls outcome data. As per recent consensus guidelines [38], falls will be defined as ‘an unexpected event in which the participant comes to rest on the ground, floor, or lower level’. Participants and carers will be given verbal and written instructions to ‘. . . record each day in weekly-returned postage paid falls diaries any fall including a slip or trip in which you lost your balance and landed on the floor or ground or lower level’; weekly telephone prompts will be used to ensure contemporaneous reporting. We have previously used this technique successfully in similar populations, with published data showing in excess of 90% return rates [39,40].

### Domain-specific quality of life

Hospital Anxiety and Depression Scale (HADS): while fear of falling is the primary outcome measure, the inter-related nature of fear of falling and anxiety mean that change in anxiety is clinically highly relevant. In addition, it is vital to assess depression in this population [10]. The HADS, though widely used, was originally validated in a population with a maximum age of 65 years [41]. However, a recent large scale UK study in four centres across England, Wales and Scotland has shown that the scale’s psychometric constructs are intact and applicable to community-dwelling older people [42].

### Generic quality of life

World Health Organization Quality of Life questionnaire-older adults module (WHOQOL-OLD) [43], EuroQol 5-dimension scale (EQ-5D), the five-level version [44] and Short Form six-dimension health survey (SF-6D) [45]: the 24-item WHOQOL-OLD is a module of the World Health Organization’s broad measure of quality of life, the WHOQOL, which was designed for adults of all ages. The WHOQOL-OLD includes additional items specific to older people. The EQ-5D is a generic quality of life measure that has the added benefits of enabling cost utility analysis (below), as does the SF-6D.

### Social participation and social isolation

Social Disconnectedness and Perceived Isolation Scales [46,47]: avoidance of social contact and social isolation are crucial co-factors both caused by, and contributing to, fear of falling. Recent work from Cornwell *et al*. has shown that the Social Disconnectedness and Perceived Isolation scales [46,47], which measure both social isolation and participation, may be particularly useful in evaluating interventions in older people.

### Impact on function

Short Physical Performance Battery (SPPB) [48-50], functional reach [51], handgrip strength [52]: the SPPB is a well-validated set of lower limb performance tests (measures walking speed over the middle 8 feet of a 12-foot course at the participant’s own ‘usual speed’, a series of chair stands to assess muscle power, plus a test of balance), which has already been used in major surveys such as the Women’s Health and Aging [50]. Performed by one trained person, the SPPB takes 10 to 15 minutes to complete, with a composite score being derived by summing the category scores for each of the three tests. Functional reach is a good indicator of confidence in balance and increased risk of having a fall, while the measurement of maximum isometric handgrip strength (using a dynamometer) has functional relevance for supporting weight (for example holding on to a stair rail). It has been included in numerous surveys, and is predictive of both disability and mortality.

Primary and secondary outcome measures are performed by research assistants in the participants’ homes or at the falls clinic.

### Health economic evaluation

The economic evaluation will address the following critical resource allocation questions:

1. From the healthcare system perspective, what are the incremental costs and outcomes (FES-I) of treatment of usual falls service care that includes CBTI over usual falls service care usual among patients with a heightened fear of falling in the short term (12 months from the start of treatment, from the trial)?

2. From a more societal perspective, what are the incremental costs and quality-adjusted life years (QALYs) of the treatment options among patients with a heightened fear of falling in the short term (12 months from the start of treatment)?

The interpretation of the economic evaluation will crucially depend upon the clinical outcome of the trial [53]. For each of 1 and 2, should the therapy result in improved outcomes and cost savings relative to normal care, then the therapy would, according to the economic evaluation, be unambiguously recommended for adoption. Otherwise, should the treatment result in both increased costs and QALYs over normal care, the incremental cost per QALY gained will be calculated, thus showing the rate of return of QALYs gained for additional resources invested.

Stochastic sensitivity analysis will be undertaken to express the uncertainty around the incremental cost per life year gained/QALY ratio based on mean costs and outcomes [54-56]. An alternative way of looking at the above issues, however, is to say that the trial has been designed as a difference trial, and, therefore, we will attempt to estimate incremental cost per QALY, focusing on the joint density of costs and effects irrespective of their precision [57]. Results will be presented in the form of cost acceptability curves, thus using net benefit criteria [58].

To assess costs, data will be collected on:

1. Intervention and other outpatient expenditures: the costs for providing the therapy will be estimated on a per patient basis. This will be derived from the total costs of providing the therapy. This will include the training time for the falls service HCAs and any additional time and resources required over the eight weeks when the therapy is delivered, as well as the cost of initial evaluation for fear of falling. Data about levels of activity will also be used to inform sensitivity analyses.

2. Resource use outside of the falls service: trial participants will be asked, during the follow-up 12-month interviews of RCT participants, about their use of primary and secondary care and other community-based services. Again, use of such services will be costed using local rates of pay and prices. The interview schedule will also include questions on private costs incurred by patients, including over-the-counter expenses and the cost of accessing medical care, such as travel expense and lost time from leisure and work activities in those who are still economically active. We also include questions about the amount of informal care provided by friends and family of people with a heightened fear of falling. The cost of this care will be estimated from equivalent professional care providers pay when applicable and by the human capital approach [59].

To generate a cost per QALY*,* data on ‘utility’ or quality of life are required in combination with data on survival. Quality-of-life data will be gathered primarily using the EQ-5D [60,61]. The EQ-5D is a generic, preference-based measure of quality of life in which ‘health’ is defined in terms of five broad dimensions. Patients will be asked to rate their health status in terms of each of these dimensions every six months (when visiting clinics for follow-up). In the UK, health states in the EQ-5D classification have been allocated scores derived from a survey of values by members of the general public (where 0 = death and 1 = full health) [62]. The SF-6D will also be used to translate outcomes measured by the SF-36 into health state utilities using of a recently produced ‘tariff’ [45]. The requisite self-response items for these quality-of-life measures will be gained through self-completion questionnaires unless the patient requires support in which case they are interviewer administered during routine visits. In the case of failure to return, these data are collected by telephone interview. As quality-of-life data are not collected on a continuous basis, power curves (simply, a form of extrapolation) can be fitted to model quality-of-life profiles for the interventions groups from baseline to end of follow-up [45]. These power curves will take account of differences in survival between the groups, so permitting generation of a QALY for each mode of care and, more importantly, a QALY difference between them.

In addition to the above, we propose to better estimate the effect on quality of life of a fear of falling. Following validation of the scale by factor analysis [63] to ensure that it adequately represents concerns about falling during social and physical activities, we will estimate the effect on quality of life of a fear of falling. We will do this by exploring the degree to which any discrepancy between EQ-5D tariff values and self-reported quality of life are explained by a fear of falling. Should the FES-I be unsuitable, we will attempt to estimate the effect of a fear of falling directly from patients by means of a standard gamble or similar preference elicitation method.

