
### Outcome data collection

Primary and secondary outcomes will be measured at baseline (pre-randomisation), at 8 weeks (that is at the end of CBTI) and 6 and 12 months post-randomisation. Assessment will also be made of harms, level of social care and dependency. Weekly symptom diaries (validated in similar populations [39,68]), completed and submitted weekly for 12 months, will record falls and injuries as described previously. Data will be collected for the purpose of the process evaluation on an ongoing basis over the course of the project.

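### The economic section's six-monthly EQ-5D conflicts with the outcome schedule, and the only QALY method described is not linked to the planned joint cost-effect analysis

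*Protocol article*

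**What the plan says.** Three parts of the protocol article bear on the timing of utility data.

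- The Generic quality of life section, within the secondary outcomes, lists the "EuroQol 5-dimension scale (EQ-5D), the five-level version" alongside the SF-6D.
- The Outcome data collection section states: "Primary and secondary outcomes will be measured at baseline (pre-randomisation), at 8 weeks (that is at the end of CBTI) and 6 and 12 months", counted from randomisation.
- The Health economic evaluation section, which describes how the QALY is made, has patients rate their health "in terms of each of these dimensions every six months (when visiting clinics for follow-up".

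On method, the economic section says that "power curves (simply, a form of extrapolation) can be fitted to model quality-of-life profiles for the interventions groups from baseline to end of follow-up". It adds that the curves take account of survival and yield one QALY per treatment option and a difference between them. Earlier in the same section, the analysis is described as "focusing on the joint density of costs and effects irrespective of their precision", with results shown as acceptability curves on a net-benefit basis. The horizon of the first economic question is set "in the short term (12 months from the start of treatment, from the trial".

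**The concern.** The two schedules cannot both describe the EQ-5D data that feed the QALY. An analyst who follows the economic section uses 0, 6 and 12 months; one who follows the outcome schedule also uses 8 weeks. The 8-week visit marks the end of weekly therapy, when an effect of the intervention on utility might be largest, so the choice can move the QALY difference.

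The second gap is between the QALY and the uncertainty analysis. A joint density of costs and effects needs the two to vary together across patients. The text goes from group profiles to a group QALY and does not say how this is paired with patient costs. Nor does it mention baseline utility, although the Statistical analysis section adjusts the primary outcome for its baseline and promises similar methods for secondary outcomes. Cost per QALY is one of the two stated economic questions, so its main inputs should be unambiguous.

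**Working it through.** **Plan's own figure.** The article gives no utility gain, QALY difference or cost-effectiveness power, so there is none to reproduce. The sample size (154 per group) concerns FES-I and has no bearing here.

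**1. Weight of each visit.** Take 8 weeks as 8/52 = 0.154 year. Under a trapezoid rule each visit's weight is half the sum of its adjacent intervals.

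- Four visits: baseline 0.154/2 = 0.077; week 8, 0.5/2 = 0.250; month 6, (0.346 + 0.5)/2 = 0.423; month 12, 0.5/2 = 0.250.
- Three visits: 0.250, 0.500, 0.250.

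**2. Effect of leaving out week 8.** Let d8, d6 and d12 be the between-arm utility differences, with none at baseline.

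- With week 8: 0.250·d8 + 0.423·d6 + 0.250·d12
- Without: 0.500·d6 + 0.250·d12
- Amount missed: 0.250·d8 − 0.077·d6

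The amount missed is zero when d8 = (8/26)·d6 = 0.31·d6, that is, when week 8 lies on the straight line from baseline to month 6. The gain is understated when week 8 lies above that line and overstated when it lies below.

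**3. Assumed gains** (none come from the documents).

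| d8 / d6 / d12 | With week 8 | Without | Shortfall |
|---|---|---|---|
| 0.02 / 0.05 / 0.05 | 0.0387 | 0.0375 | 3% |
| 0.05 / 0.05 / 0.05 | 0.0462 | 0.0375 | 19% |
| 0.05 / 0.03 / 0.03 | 0.0327 | 0.0225 | 31% |
| 0.05 / 0.03 / 0.02 | 0.0302 | 0.0200 | 34% |
| 0.05 / 0.02 / 0.02 | 0.0260 | 0.0150 | 42% |
| 0.05 / 0.025 / 0 | 0.0231 | 0.0125 | 46% |
| 0.05 / 0 / 0 | 0.0125 | 0 | 100% |

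**4. What the table does not measure.** It compares one trapezoid with another, while the plan names power curves. As an illustration, a curve a·t^b put through equal gains of 0.03 at 6 and 12 months has b = 0 and area 0.030. The four-visit trapezoid for a constant 0.03 gives 0.0277 and the three-visit trapezoid 0.0225. So the curve need not err in the same direction as the three-visit trapezoid. The article gives no form for the curve, and its error was not computed.

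**5. Can a group-level QALY support a joint density?** For a linear rule with complete data, the area under the mean profile equals the mean of the patients' areas: Σ w_j·(mean of u_ij over i) = mean over i of (Σ w_j·u_ij). Resampling patients with their costs and recomputing the group profile must then agree with patient-level QALYs. A simulation with assumed utilities and costs, 154 per arm and no missing data confirmed this: cost-effect correlation −0.345 both ways, and probability of positive net benefit at 20,000 per QALY of 0.419 both ways. Breaking the pairing gave 0.427, so in that example pairing mattered little to this probability. The identity is not guaranteed for a non-linear curve or with missing data, and the Sample size section allows for 25% drop-out.

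**The case against.** Much can be said for the plan. The article condenses a fuller protocol, and details of a health economic analysis may properly sit in a plan that is not shown.

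- **Week 8.** A reader might infer that the 8-week EQ-5D is lost. The text does not support that: the secondary outcome list and the outcome schedule together place EQ-5D at 8 weeks, and the economic section nowhere says that the curve must exclude it. What stands is a conflict between sections.
- **Patient-level QALYs.** A reader might infer that none can exist. EQ-5D is completed by each patient, and the curves "can be fitted to model quality-of-life profiles for the interventions groups from baseline to end of follow-up", which is permissive. A patient-level QALY is undescribed, not excluded. Step 5 shows that a joint density can be had without one if patients are resampled with their costs and the curves refitted each time. What stands is that the article describes neither route.
- **Time origin.** A reader might infer that the arms are counted from different dates, because the horizon runs from the start of treatment. No section sets different origins, assessments are timed from randomisation in both arms, and the control arm is itself described as treatment as usual. This is loose wording only.
- **Early peak.** The Background reports that FES gains after one group programme faded, but also that fear of falling still differed between arms at 14 months in another group trial. Neither is utility, and a reinforcement session is planned. An early peak in EQ-5D is possible, not shown.
- **Baseline utility.** Chance imbalance is not bias under randomisation. Adjustment is a matter of precision and of the estimate in hand, and it is neither stated nor ruled out.

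**Conclusion.** The point holds in limited form. The EQ-5D schedule in the economic section contradicts the outcome schedule, and following the economic section as written would leave the end-of-therapy value out of the QALY. The only QALY construction described is an optional group-level curve, with no stated link to patient costs and no stated adjustment for baseline utility.

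The size is conditional. Under a trapezoid rule, no baseline difference and the assumed gains above, omitting week 8 lowers the QALY gain by about 3% when benefit builds up, by up to 46% when it fades to nothing by 12 months, and by 100% when it exists only at week 8. These percentages should not be read as the error of the planned analysis, which names a different curve. The matter concerns the economic evaluation and leaves the primary FES-I comparison untouched. It is worth correcting because the cost is small.

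**What to change.** - In Health economic evaluation, replace the six-monthly statement with the schedule in Outcome data collection ("at 8 weeks (that is at the end of CBTI) and 6 and 12 months post-randomisation", plus baseline), and state that EQ-5D and SF-6D from all four assessments enter the QALY.
- Compute each patient's QALY as the area under that patient's utility profile.
- Compare arms by regression on arm, baseline utility and the stratification factors.
- Resample each patient's QALY together with the same patient's costs to obtain the joint density and acceptability curves. If group curves are kept, say that patients are resampled with their costs and the curves refitted in every resample.
- As a clarification of wording only, give the horizon as 12 months from randomisation, matching the outcome schedule.

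The cost is slightly more analysis work and, if EQ-5D and SF-6D are not already given at 8 weeks, a short questionnaire at a visit that already takes place. For patients already past that visit without it, the value cannot be recovered, and the report should say so.

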### Qualitative process evaluation of the trial

The purpose of the process evaluation is to understand the organizing processes that underpin delivery of the trial and its reception by professionals and patients, we will undertake an ethnographic sub-study within the trial. May and colleagues have employed these methods previously [64-66]. The aim of the study is therefore to identify, describe, and explain the professional and organizational factors that promote or inhibit the implementation and integration of the intervention.

Throughout the study we will track the activities of key personnel and their interactions with each other as the trial develops. We will examine the implementation of the intervention by a rolling programme of interviews with members of the trial team (maximum n = 15), along with observations of team and other relevant meetings (n = 9 approximately), that focus on the delivery and take up of the intervention by participating health professionals and service users. We will interview all professionals involved in intervention development and service delivery (n = 7 approximately) including clinical and related professionals who will be able to contribute different perspectives. Professionals will be interviewed at multiple time points across the duration of the study, but we will utilise brief follow-up telephone interviews of these individuals to explore how the evaluation and interpretations of the intervention changes over time without overburdening individuals. The range, flexibility and depth of ethnographic research is a significant advantage in such work, and represents the only way such a project could be undertaken. We will interview a purposive sample of patients (n = 10 during Phase 1; n = 20 during Phase 2) focusing on their views/experiences of the intervention and factors affecting normalisation from their perspective. In all cases, interviews and observations will be undertaken only when informed consent has been obtained and recorded from participating researchers, patients, and health professionals. To reduce the burden of research, interviews with participating patients will not exceed 45 minutes duration without their express permission. All interviews will take place at a time and location of the interviewee’s choosing. Meetings and interviews will be audio recorded using digital voice recorders. Audio recordings will be transcribed, checked, and edited to ensure participants’ anonymity (with particular attention to removing identifying data from professionals’ transcripts). Transcripts will be stored in password-protected computer systems, and non-anonymised voice recordings or transcripts will be handled only by members of the research team and transcribers who have signed appropriate confidentiality agreements. We will use Normalization Process Theory as a conceptual framework from which to develop a structured qualitative analysis of the transcript data set using the Framework method pioneered by Ritchie and Spencer [67]. This analysis will lead to a robust conceptual model of the factors that have affected the course of the intervention. This model will be of value to other clinicians and researchers wishing to deploy the intervention since it will provide a guide to implementation, embedding, and integration in everyday clinical practice.
